### Measures used to achieve objectives

#### Primary objectives

*Willingness of women to be randomised into the control or intervention group*
The measure used to assess this objective will be assessed by the midwife in the birthing unit, and once the woman has an epidural in situ, the woman will then be consented by the midwife. The midwife will then access the sealed opaque envelopes that allocate the woman to the group using the peanut ball or the group receiving standard care and not using the peanut ball (this has been generated by the computer software: sealedenvelope.com). The midwife will have no previous knowledge of which group the woman will be allocated to until the envelope is opened (allocation concealment). If the woman has been allocated to the group not using the peanut ball and she decides she wants to use the peanut ball, the woman’s reasons for using the peanut ball will be noted and the midwife will notate this in the Peanut Ball Research Notebook that accompanies the boxes for information and consent and the allocation box in the birthing suite. The Coordinating Investigator will liaise and visit contacts at both sites for this information.
*Estimation of recruitment and attrition rate*
Acceptability of the recruitment methods will be assessed including any adverse events recorded whilst using the peanut ball during labour (these details will be accessed via the Electronic Medical Record or woman’s progress notes during labour by the coordinating investigator). The main method of recruitment of the women will be midwives working in the birthing unit, identifying and approaching the woman, as they have been previously educated about the research project by education sessions and an education package has also been written for the midwives about using the peanut ball for the research project provided by the coordinating investigator. Sample size analysis should be adequate to estimate the recruitment rate [18]. Modifications may be made to the protocol for the full trial based on recruitment rates.
*Estimation of women staying in allocated group*

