Midwives will record in the Peanut Ball Research Notebook in the birthing unit if the woman changes her mind if she is allocated to the control or intervention group and decides to change to the other group other than the group she has been allocated. It is important to achieve an “intention to treat analysis” and that participants are analysed according to the group they are originally allocated [19].
*To determine why women stopped using the peanut ball*
The Coordinating Investigator will access the Electronic Medical Record to assess why the woman stopped using the peanut ball. It is important to achieve an “intention to treat analysis” to determine whether or not they adhered to or accepted the intervention. The importance of reporting of numbers and the reasons why participants were lost to follow up is necessary to assess the extent to what the intention to treat may lead to and provide an underestimate of the efficacy of the intervention under ideal circumstances [19].
*To assess likely primary and secondary outcome measures to inform sampling size and powering of the definitive RCT*
The main purpose of this pilot study is to assess the feasibility of conducting a full definitive trial and not to generate statistically significant results. Nonetheless, a secondary aim is to inform the sample size calculation to design a full definitive trial. This requires an estimate of a clinically meaningful effect size and variance that can be entered into a sample size calculation. The key primary clinical outcome is the rate of vaginal births, and the key secondary outcome is the length of labour. For this pilot study, a decision was taken to opt for 50 pregnant women (25 in each trial arm) to inform this process. Indeed, a previous pilot study that investigated the use of the peanut ball with similar aims determined that this sample size may actually be sufficient to demonstrate statistically significant findings [13]. Therefore, given the high feasibility of recruiting these numbers of women at the study sites, a decision was then made to aim for 50 pregnant women in total (as a minimum), and so opt for a comprehensive pilot trial to ensure the pilot can confidently test feasibility and also inform the powering of a future definitive trial.

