### Statistical analysis

#### Quantitative data

In terms of the women’s willingness of being randomised into the control or intervention group and assessment of recruitment and attrition rates and staying in the allocated groups, the Coordinating Investigator will access this information from the Peanut Ball Research Notebook and assess the sample size. This information will be estimated as accurately as possible from the critical parameters we wish to estimate [19, 22] that includes the minimum important differences when comparing the means of continuous outcomes and categorical outcomes between the intervention and control groups. The differences between the vaginal birth rate (assessment of likely primary outcome for definitive RCT) and the length of labour (assessment of likely secondary outcome for definitive RCT) will be analysed. Demographics will be reported using descriptive statistics. The Coordinating Investigator will also access women lost to follow up and if women stopped using the peanut ball from the Electronic Medical Record.

The purpose of the pilot is to assess the feasibility of the component elements together to inform a definitive trial. The pilot and sample size of 50 is not intended to be powered to conduct meaningful statistical tests [19]. Nonetheless, and for exposition purposes, standard tests will be conducted and reported. Online survey results will provide complementary data from the woman’s perspective of using the peanut ball during labour and health and quality of life.

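### Whether and why women stopped using the ball is read from the medical record alone, so stops that are not a change of group may be missed and adherence overstated

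*Protocol article*

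**What the plan says.** Under Objectives, Primary objectives, the protocol article lists five aims. One is "To determine why women stopped using the peanut ball". A separate aim is to estimate how many women remain in the group to which they were allocated.

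Under Measures used to achieve objectives, Primary objectives, each aim is given a source:

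- **Reasons for stopping:** "The Coordinating Investigator will access the Electronic Medical Record to assess why the woman stopped using the peanut ball".
- **Remaining in group:** "Midwives will record in the Peanut Ball Research Notebook in the birthing unit if the woman changes her mind". The event that prompts this entry is that she "decides to change to the other group other than the group she has been allocated". It applies to both arms.
- **Control women who want the ball:** here "the woman’s reasons for using the peanut ball will be noted", and the midwife writes this in the same notebook.

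Statistical analysis, Quantitative data, keeps the same division. The notebook supplies willingness, recruitment, attrition and adherence to group. For stopping it says: "The Coordinating Investigator will also access women lost to follow up and if women stopped using the peanut ball from the Electronic Medical Record".

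**The concern.** The plan has an instrument at the bedside, filled in by the person who sees the event. For stopping the ball it relies instead on later reading of the medical record. The notebook asks about a decision to change group, and coming off the ball is not necessarily such a decision. A woman may stop because of discomfort or a clinical event, or because the ball was not replaced after she was moved.

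The sources are also asymmetric. Reasons are noted at the time for a control woman who takes up the ball, but no matching entry is described for a ball-arm woman who stops. Yet stopping in the ball arm is the event the primary objective concerns.

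The article says this information is needed to judge whether women adhered to and accepted the intervention. If stops are missed, the error runs one way, towards better apparent adherence, and the reasons cannot be reliably recovered after the birth. The definitive trial would be planned on that figure.

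**Working it through.** **No figure to reproduce.** The article states no expected stopping rate. The sample of 50 is described as a decision, not the result of a formula. The check is therefore a comparison of sources, followed by an illustration.

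**Step 1: which events each source captures, as described.**

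| Event | Notebook entry described? | Source of the reason |
|---|---|---|
| Control woman wants the ball | Yes | Notebook |
| Ball-arm woman decides to change group | Yes | Electronic Medical Record |
| Ball-arm woman stops, no decision to change group | No | Electronic Medical Record |
| Ball-arm woman continues | No | Not applicable |

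The last two rows differ only by what the medical record happens to contain. If it says nothing about stopping, the two women cannot be told apart, and the third can be counted as having stayed in her group. The Peanut ball section calls for a change of position every 30 minutes during use, so there are repeated moments at which the ball might come out and not go back.

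**Step 2: what one missed stop does.** With the planned minimum of 25 women in the ball arm, 1/25 = 4 percentage points.

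**Step 3: illustration.** Let p be the true proportion stopping and c the share of stops that the record shows. Neither is in the article. The assumed ranges are p = 20% to 40% and c = 50% to 100%.

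- Recorded stopping = p × c
- Apparent adherence = 1 − p × c
- Overstatement = p × (1 − c)

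| True stopping p | True adherence | Apparent, c = 90% | Apparent, c = 70% | Apparent, c = 50% |
|---|---|---|---|---|
| 20% (5 of 25) | 80% | 82% | 86% | 90% |
| 30% (7.5 expected) | 70% | 73% | 79% | 85% |
| 40% (10 of 25) | 60% | 64% | 72% | 80% |

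The overstatement runs from 0.20 × 0.10 = 2 points to 0.40 × 0.50 = 20 points. It is 0 when c = 100%.

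**Step 4: set against sampling error.** Suppose 8 of 25 truly stop: 32%, exact (Clopper-Pearson) 95% interval 14.9% to 53.5%.

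- If the record shows three quarters of them, the pilot reports 6/25 = 24% (9.4% to 45.1%).
- If it shows half, the pilot reports 4/25 = 16% (4.5% to 36.1%).

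The intervals overlap heavily, so the bias could not be seen in the pilot's own data. Unlike sampling error, it would not shrink with more women.

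**The case against.** The strongest reply is that under-recording is assumed, not shown. The article says nothing about how complete the record is on ball use, or whether it has a field for it. The midwives receive education sessions and a written package about the project. The full protocol is a supplementary file that is not shown and may contain a data collection form. If charting is complete, there is no bias. This stands as to certainty and size: a reader might infer that stops will be under-counted, and the article supports only that they may be. It does not remove the point, because the article does not leave the source open. It names the medical record for stopping in two places and names no other.

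Three further stronger readings are tempting and are not supported.

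- **Timing as part of the objective.** A reader might infer that when women stopped is a primary objective. Only the reasons are named.
- **The notebook as a log of changes of mind only.** Quantitative data also draws willingness, recruitment and attrition from it. A ball-arm woman who no longer wants the ball could reasonably be entered as changing group, since the control arm is defined by not using it. The gap is confined to stops without such a decision.
- **Two primary objectives resting on the medical record.** Remaining in the allocated group is taken from the notebook. It is affected only in part, through stops that the notebook's trigger does not reach.

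The satisfaction survey asks about discomfort and positions used, and maternal position in labour is a collected outcome. Both give some information on use. Neither is described as recording that the ball was stopped, or why, and the survey depends on women responding.

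**Conclusion.** The point holds as a weakness in a stated method. The medical record is the only named source for whether and why women stopped, and the notebook's adherence entry depends on a decision to change group. Stops without that decision may be missed, and if they are, adherence is overstated and their reasons are lost.

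The size cannot be fixed from the article: 4 points per missed stop among 25 women, and 2 to 20 points if 20% to 40% stop and the record shows 90% to 50% of stops. All those stopping and capture rates are assumptions. The direction is certain only on the condition that stops are missed. The change is worth making because it protects a primary objective at very small cost and, as Trial status reports, recruitment has not begun.

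**What to change.** For every woman allocated to the ball, have the midwife complete one line in the existing Research Notebook at the time: ball started (yes/no), ball stopped before birth (yes/no), and the reason for stopping, with categories such as the woman's choice, discomfort, clinical event, or other with free text. Time of stopping is optional, since the objective does not ask for it. Because a line is required for every ball-arm woman, a blank shows as missing data and is not read as continued use.

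Amend Measures used to achieve objectives and Quantitative data so that the notebook is the primary source for stopping and the Electronic Medical Record is the cross-check. Report stopping and its reasons over all women allocated to the ball.

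The cost is a few seconds of midwife time per woman and one added item in the education package. Clinical care is unchanged.

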#### Secondary objectives

*To investigate completion of the health and satisfaction surveys*

Health and satisfaction surveysThe Health Questionnaire (EQ-5D) will provide important general physical and mental health information about mobility, self-care, usual activities, (for example, work, study, housework, family or leisure activities), pain, discomfort, anxiety, and depression. EQ-5D is a standardised measure of health status developed by the EuroQol Group in order to provide a simple, generic measure of health for clinical and economic appraisal. The EuroQol Group is a network of international multidisciplinary researchers devoted to the measurement of health status [20]. The Health Questionnaire will also request a single score about level of health experienced on that particular day. The first five questions are measured on a Likert scale, and the last question about perception of health asks the respondent to answer on a scale from 0 to 100 with 0 meaning the worst health they can imagine and 100 meaning the best health they can imagine. It is cognitively undemanding, taking only a few minutes to complete. The survey is applicable to a wide range of health conditions and treatments; it provides a simple descriptive profile and a single index value for health status that can be used in the clinical and economic evaluation of health care as well as in population health surveys. The EQ-5D is designed for self-completion by respondents and is ideally suited for use in postal surveys, in clinics and in face-to-face interviews [20].The survey assessing satisfaction levels obtains information in 13 questions about using the peanut ball in Likert scale responses, yes/no answers and free text responses and takes approximately 5 min to complete. The survey will provide a snapshot about the woman’s experience and enquire about the benefits of using the peanut ball, subsequent use of the peanut ball, whether the woman would recommend using the peanut ball to other women and reasons why, discomfort, specific positions used with the peanut ball, experiencing feelings of empowerment and effect on length of labour and demographic details. The survey was developed in alignment with the results of the previous randomised controlled trials [13–15] and as this research only focuses on quantitative data, it was thought that it was beneficial to obtain some information from women about the comfort, perception and satisfaction about using the peanut ball as complementary evidence to the pilot randomised controlled trial. Face validity has been verified by this survey being reviewed and approved by an ethics committee of expert health research professionals in a local health district in NSW, and the survey will be further validated in this pilot study by comparing responses from both sites by using construct validity and establishing appropriate sample size.
Both surveys will be distributed to the respondents from an electronic platform—Qualtrics [21] platform—and have been electronically tested to assess the functionality prior to distribution of the online survey. Each survey will be distributed to the participant’s email and de-identified in the computer database. All surveys will be analysed, including those not completed. All of the data collected in this closed survey will be stored in a password-protected computer and will only be accessible by the researchers.
*To assess the feasibility of conducting an economic evaluation alongside a future definitive trial*
The feasibility of collecting data required for an economic evaluation will be tested. For this pilot, we will collect information on health service usage between trial arms, including staff time, medications, procedures and length of stay in hospital. The inclusion of the EQ5D5L will assess the feasibility of incorporating an economic measure of HRQoL, where responses will be converted into ‘health utilities’.
*To measure key clinical outcomes and differences between the control and intervention group*
Details about other birth outcomes will also be collected to determine the baby’s condition, perineal damage, other methods of pain relief used, position of mother and baby during labour, blood loss, cervical dilatation at time of insertion of epidural and evidence of augmentation and/or induction of labour.

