## Discussion

The peanut ball is a non-pharmacological method of pain relief that may be used by women using epidurals in labour, and preliminary randomised controlled trials in the USA have shown clinically and statistically significant findings. Currently, peanut balls are being used by women during labour, in hospitals in Australia; however, there is no existing evidence that the peanut ball makes a difference for women, either as a birthing ball or whilst using an epidural. It is important to fully investigate the potential benefits of using the peanut ball in Australia, especially when we are now working with increased rates of caesarean sections [23].

The web-based survey about the woman’s general health will provide general physical and mental health information about mobility, self-care, usual activities, pain, discomfort, anxiety and depression. We would expect that this cohort of pregnant women with low-risk pregnancies will provide a result of a generally healthy population. The web-based survey about using the peanut ball will provide a snapshot of information about the woman’s level of satisfaction, positions she used, her perception about influencing the length of labour, level of empowerment and whether she would recommend the peanut ball to other women using epidurals during labour. Demographics will also be collected. Expected results in the overall context of the study would show that the peanut ball has benefits for women using epidurals in labour, not only in her positive perception and feeling of empowerment but also increasing her comfort.

This study will be the first to investigate the pilot effect of the peanut ball for women using epidurals in labour in a low-risk maternity model of care in Australia. It is expected that the mean clinical and health service outcomes will improve in the peanut ball arm. If the results point to reject using the peanut ball and no benefits are found, it is expected that midwives will continue to suggest using the peanut ball to increase comfort and empowerment for women using epidurals in labour. The pilot trial will inform the development of a fully powered definitive trial to assess the clinical meaningful and statistically significant outcomes, including an economic evaluation to assess cost effectiveness.

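### Table 1 schedules the EQ-5D at one undated postnatal point, so the pilot does not test the dated, repeated collection that a utility-based economic evaluation would need

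*Protocol article*

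**What the plan says.** All references are to the Protocol article.

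- **Instrument.** Under Measures used to achieve objectives, Secondary objectives, the EQ-5D has five dimension questions and a 0 to 100 rating. On the index, "it provides a simple descriptive profile and a single index value for health status". On the rating, "The Health Questionnaire will also request a single score about level of health experienced on that particular day".
- **Delivery.** The same section says "Each survey will be distributed to the participant’s email and de-identified in the computer database". It gives no send day, reply window or repeat. It also says that incomplete surveys will be analysed.
- **Timing.** Table 1, the participant timeline, has one survey column, and its timepoint is simply postnatal. There is no baseline EQ-5D and no second survey column.
- **Economic objective.** "The inclusion of the EQ5D5L will assess the feasibility of incorporating an economic measure of HRQoL", with responses converted to utilities. For resource use, "we will collect information on health service usage between trial arms, including staff time, medications, procedures and length of stay in hospital". The Discussion says that the definitive trial will include a cost-effectiveness assessment.
- **Who is surveyed.** The Background has all women reporting on general health. Setting, recruitment and informed consent describes recontact for an online survey only for women who used the ball.

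**The concern.** Utilities usually enter an economic evaluation as health over a period, which takes readings at known times. For this population the uncertain part is whether women with a newborn will answer on set days, and answer again later. One postnatal survey does not inform that.

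The timing of a single reading may also matter. The Background says that women who have a caesarean may need more help after birth. The EQ-5D covers mobility, self-care, usual activities and pain, and vaginal birth rate is the key clinical outcome. Any effect of the ball on utility could therefore run through mode of birth and be largest early. A reading without a fixed day may catch or miss that period.

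At stake is how useful the pilot's answer on economic feasibility will be when the definitive trial's follow-up is designed.

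**Working it through.** The article gives no figure for EQ-5D timing, utilities or their variability, so there is nothing of its own to reproduce. The check has three parts.

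**1. What a single wave does estimate.** The planned minimum is 50 women, 25 per arm. The Wilson 95% interval for a completion proportion p out of n, with z = 1.96, is

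[p + z²/(2n) ± z·√(p(1−p)/n + z²/(4n²))] / (1 + z²/n).

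Taking illustrative counts:
- 35 of 50 complete: (0.7384 ± 0.1327)/1.0768, or 0.56 to 0.81.
- 18 of 25 complete in one arm: 0.52 to 0.86.

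So first-contact completion is estimated, if imprecisely. Nothing in Table 1 yields the same quantity for a second contact.

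**2. How far one utility could depend on reply day.** All values here are assumptions. Let utility rise in a straight line to 0.9 over 42 days, equally in both arms. The shift in mean utility is then total rise / 42 × gap in mean reply day.

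| Assumed rise over 42 days | Per day | 7-day gap | 14-day gap |
|---|---|---|---|
| 0.10 (from 0.8) | 0.0024 | 0.017 | 0.033 |
| 0.20 (from 0.7) | 0.0048 | 0.033 | 0.067 |
| 0.30 (from 0.6) | 0.0071 | 0.050 | 0.100 |

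If recovery took 14 days instead, a 7-day gap within that period would shift the mean by 0.10/14 × 7 = 0.050 to 0.30/14 × 7 = 0.150.

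**3. What one reading says about health over the period.** Carry a single utility u across 42 days as u × 42/365.25 and compare it with the area under the assumed line.

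- Rise from 0.6 to 0.9: a day-1 reply (0.607) gives 0.0698 and a day-42 reply (0.900) gives 0.1035. The area is 0.75 × 42/365.25 = 0.0862.
- Rise from 0.8 to 0.9: a day-1 reply (0.802) gives 0.0923 and a day-42 reply gives 0.1035. The area is 0.85 × 42/365.25 = 0.0977.

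One reading therefore does not fix health over time unless the shape of recovery is assumed, and the error depends on that shape.

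**The case against.** The best defence is that this is a condensed article. The full protocol is an additional file that is not shown, and a send day, a reply window and a study-number link are details an article may leave to it. The stated aim is modest: to see whether the data can be collected. No QALY is named for the pilot or the later trial. Statistical analysis singles out vaginal birth rate and length of labour, treats survey results as complementary, and disclaims meaningful tests at 50 women. Nothing in the article suggests that reply day would differ by arm, and every input in parts 2 and 3 of the working is assumed.

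Much of this stands. Silence on the send day and window is not by itself a fault. The number of survey waves is different, because a participant timeline exists to state it, and Table 1 states one.

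A reader might infer more than the article supports:

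- **That the design cannot test economic feasibility at all.** Completion, conversion to utilities and resource-use capture are tested and match the stated objective.
- **That the sentence on that day's health shows utilities depend on reply day.** It describes the 0 to 100 score. Utilities come from the separate index, and the article states no recall period for the five items. Dependence on reply day follows only if health changes after birth.
- **That survey data cannot be joined to arm or cost.** The phrase "email and de-identified in the computer database" does not mean unlinked.
- **That a ceiling is established.** "We would expect that this cohort of pregnant women with low-risk pregnancies will provide a result of a generally healthy population" is an expectation about a low-risk cohort. It makes the ceiling share worth reporting but does not demonstrate one.

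**Conclusion.** The point holds in a limited form. As scheduled in Table 1, the pilot tests one postnatal survey, conversion to utilities and capture of resource use. It does not test the dated, repeated collection that a utility-based evaluation in the definitive trial would need. If health changes in the weeks after birth, the single utility also depends on when the woman replies.

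The size of that dependence is unknown. The range of 0.017 to 0.050 for a 7-day gap rests on an assumed linear recovery of 0.10 to 0.30 over 42 days, and a bias between arms would further require reply days to differ by arm. The conclusion also assumes that the full protocol does not schedule a second wave that Table 1 omits.

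The conflict over who is surveyed needs no such assumption. If the recruitment section governs, utilities from women who did not use the ball, and so most or all of the control arm, would be missing.

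**What to change.** In Table 1 and in the survey and economic text under Measures used to achieve objectives, Secondary objectives:

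1. Send the EQ-5D-5L to all randomised women in both arms at two fixed times counted from birth. The team should choose the times, for example the first week and about six weeks.
2. Record the completion date of each reply.
3. Report completion, and the share with no problems on all five dimensions, by arm and timepoint.
4. Keep late replies and report them with their dates. Dropping them would conflict with the statement that all surveys are analysed.
5. Reconcile Setting, recruitment and informed consent with the Background so that control-arm utilities are collected. The satisfaction survey can remain for women who used the ball.

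The cost is one extra automated email from the platform already in use, a few minutes per woman and a small amendment. Trial status says that recruitment has not begun. Completion will probably be lower at the second wave, and that figure is what the definitive trial needs to know.
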